## Abstract

**Background:**

Uveal melanoma is the most common primary intraocular tumor in adults. In Sweden, at least 100 patients are diagnosed with the disease each year. Almost half of the patients develop metastases, with a median survival time of 1 year once metastases are detected. The primary ocular tumor is typically treated with either enucleation or brachytherapy, and no adjuvant treatment is added. Melatonin is an indolamine hormone that has improved survival in previous trials with patients diagnosed with various cancers, including advanced cutaneous melanoma. Side effects have been mild. We aim to investigate if adjuvant treatment with melatonin for 5 years following diagnosis of non-metastasized uveal melanoma can decrease the occurrence of metastases.

**Methods:**

An open-label, prospective, 5-year randomized clinical trial (RCT) will be conducted at St. Erik Eye Hospital. One hundred patients recently diagnosed with non-metastatic uveal melanoma will be randomized to either treatment with adjuvant melatonin 20 mg (4 tablets of 5 mg) at 10 pm for 5 years, or to standard follow-up (control group). The primary outcome measurement is the relative risk for having developed metastases 5 years after randomization. The secondary outcomes are overall survival, risk of developing other cancers, overall survival after detection of metastases, and differences in the occurrence of adverse events (AE) and serious adverse events (SAE) between the groups.

**Discussion:**

Melatonin has been found to positively impact our immune system, inhibit angiogenesis, stimulate apoptosis in malignant cells, and act as a potent antioxidant. Previous clinical trials have used similar doses of melatonin with positive results, particularly in advanced stages of cancer. Previous animal and human studies have found the toxicity of the hormone to be low. Considering the potential benefits and limited risks of melatonin, as well as its global availability, it may be a suitable candidate for an adjuvant treatment in patients with uveal melanoma.

**Trial registration:**

Our trial protocol has been approved and registered by the Swedish Medical Products Agency on June 22, 2022 (EudraCT 2022–500,307-49–00). Our trial registration number is NCT05502900, and the date of registration is August 16, 2022.

## Administrative information

In this trial, 100 subjects with non-metastatic uveal melanoma will be randomized to either treatment with melatonin 20 mg at 10 pm for 5 years or to a control group. The main objective is to investigate whether treatment with melatonin can reduce the risk of developing metastases after 5 years. Only subjects at high risk for metastasis development will be included in the trial. As uveal melanoma has a relatively low incidence rate compared to other cancers, the recruitment period is estimated to take 3 to 4 years.

## Introduction

### Background and rationale

About 50% of patients diagnosed with uveal melanoma develop metastases, primarily in the liver [1]. This risk is consistent regardless of which method is chosen to treat the primary tumor [2]. The most common forms of treatment include enucleation (surgical removal of the tumor-containing eye), proton beam irradiation, and plaque brachytherapy—a form of local radiation treatment. Due to very early seeding of micrometastases, the treatment choice typically does not affect the risk of dying from metastatic disease. Micrometastases are clusters of cancerous cells too small to be detected in standard radiological examinations, which migrate from the primary tumor to other organs, such as the liver, where they can remain latent for many years before growing into radiologically detectable tumors, or macrometastases [3]. By the time these metastases are detected, the median survival time is 1 to 2 years [4, 5]. This project’s objective is to investigate if adjuvant treatment with melatonin tablets, following diagnosis of the primary tumor, decreases the risk of developing macrometastases of uveal melanoma.

Previous randomized, placebo-controlled trials investigating various types of solid cancers including cutaneous melanoma have found that melatonin can improve 1-year survival [6]. A similar impact has been seen in a smaller study, where partial responses or stable disease progression was found in 12 of 40 patients (30%) with advanced cutaneous malignant melanoma taking melatonin after an average follow-up of 5 weeks [7]. In a third study, adjuvant treatment with melatonin following surgical resection of lymph node metastasized cutaneous malignant melanoma resulted in significantly fewer patients with progression after an average of 31 months compared to the placebo group [8]. No melatonin-related toxicity was detected in the treatment groups. In a recently published trial with patients with non-small cell lung carcinoma, a significantly improved progression-free survival was seen in a subgroup of patients with advanced-stage disease; however, in another, similar study, no such impact was seen after a year of treatment with melatonin [9, 10]. The overarching factor responsible for melatonin’s impact on cancer is believed to be related to its oncostatic properties, including inhibition of tumor cell proliferation, remodeling of the cytoskeleton, antioxidative effects, and stimulation of the immune system [11–13].

We have recently described the rationale for adjuvant treatment with melatonin for uveal melanoma in a review of the literature [14]. Studies from 1997 and 1998 showed that melatonin can inhibit the growth of uveal melanoma cells with 41 to 50% in a concentration of 0.1 to 10 nM, compared to non-treated cells [15, 16]. Melatonin’s precursors tryptophan and serotonin have not shown a similar effect [16]. Moreover, uveal melanoma could express transmembrane receptors for melatonin. In a study performed by Roberts et al*.*, melatonin and its membrane receptor agonists (MT1 and MT2) were found to inhibit the growth of uveal melanoma cells at low concentrations without impacting non-cancerous melanocytes [17].

In animal studies, the effects of melatonin on uveal melanoma have varied. In a study performed on mice, the cell-line B16-F10 was injected in the tail vein of melatonin knockout mice which were then treated with melatonin 20 mg/kg. After 15 days, there were no significant differences in the number and size of lung metastases compared to controls [18]. Another study performed on a human melanoma xenograft mouse model which was injected with DX3 melanoma cells while receiving injections of melatonin or melatonin analogs UCM 1033 and UCM 1037. When measuring tumor size both 4 weeks after treatment and after euthanization, the injections of UCM 1033 and UCM 1037 were found to inhibit tumor growth by 40 and 90% respectively, while melatonin provided no significant tumor growth suppression [19]. Another study found that mice which received 5 μg/g melatonin in their drinking water daily at the time of melanoma inoculation had a lower size and weight of their melanoma compared to control groups 40 days after administration [20]. In a similar study, athymic mice were injected with melanoma cells and received either 5 μg/g body weight of melatonin in their drinking water together with 0.5% ethanol, 0.5% ethanol alone, or neither melatonin nor ethanol. After 40 days, the mice treated with melatonin had tumors lower in both size and weight [20].

A meta-analysis published in 2005 suggested that melatonin may have similar therapeutic effects in humans. Results found that melatonin treatment in patients with solid tumors was associated with a 44% reduction in the risk of death at 1 year [6]. A clinical trial published in 1991 investigated the effects of melatonin treatment in 40 patients with advanced malignant melanoma, of which, 10 had uveal melanoma [7]. Participants were given oral melatonin in doses ranging from 5 to 700 mg/m^2^ four times a day. After a median follow-up time of 5 weeks, twelve patients showed a response or stable progression of disease. The response appeared to depend, however, on the dose, type of melanoma, and metastasis location with a dose of 75 mg/m^2^ having the best effect with minimal side effects, primarily fatigue [7]. Another clinical trial including five patients with metastatic melanoma studied the effect of adjuvant treatment with 50 mg melatonin taken orally. While four of the five patients had no response to the therapy, one patient continued taking melatonin for over 8 months and had almost total cancer regression [21]. To date, there have been no earlier studies of the long-term effects of melatonin on human patients with uveal melanoma.

## Methods

### Trial design

The study is an open, randomized intervention study without a placebo control. One hundred patients will be randomized to either treatment with melatonin 20 mg at 10 pm, or before bedtime (melatonin group), or to standard follow-up (control group) for a period of 5 years. Aside from treatment with melatonin in the melatonin group, all participants will follow the same schedule for controls and follow-ups as other patients with uveal melanoma. Follow-up examinations are planned 1, 3, 6, and 12 months after primary tumor treatment with either surgery or brachytherapy, followed by annual or semi-annular examinations for life. Radiological examinations, usually with contrast-enhanced ultrasound or computed tomography, are performed every 6 months during the first 5 years. The population treated with melatonin will later be compared to the control group regarding the primary and secondary outcomes.

There are three reasons why we are not using a placebo in this study:

First, our most important outcomes are determined by the results of the radiological examinations (i.e., whether or not metastases are detected), which leaves little room for the placebo effect. Second, the standard clinical routine for uveal melanoma patients is not to use adjuvant treatments after the primary tumor treatment, but instead monitor patients with regular radiological follow-ups. This routine is currently practiced internationally, with little variation between countries. Third, the risk of metastases and survival in the control group are already well known since it has remained consistent over the past several decades with little variation between different populations and time periods [1, 22–35]. It is therefore relatively straightforward to compare our control group to previous cohorts that have not received placebo. Therefore, we will be able to confirm that our control group is representative of bigger populations. This comparison would be more difficult if the control group were to receive a placebo.

### Study objectives and hypothesis

The primary objective of this trial is to investigate whether adjuvant treatment of non-metastatic uveal melanoma with melatonin 20 mg each night reduces the occurrence of metastasis 5 years after randomization (relative risk). The outcome will be measured once the last person in the trial has taken their last melatonin tablet. The secondary objectives for the trial are to examine if adjuvant treatment with melatonin 20 mg each night for 5 years after randomization can:Improve overall survival in 5 yearsReduce the hazard of developing another type of cancer in 5 yearsImprove overall survival after metastasis detectionExamine if the occurrence of AE and SAE differs between the melatonin and control groups.

When the last recruited patient has been treated with melatonin for 3 years, interim analyses will be performed. At this point in time, we will compare the occurrence of metastases as well as the overall survival in the melatonin and the control group.

Our hypothesis, based on previous research, is that the group treated with melatonin will have a lower relative risk (RR) for metastasis 5 years after randomization.

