### Sample size

Our power calculations will be based on the following:A previously calculated metastasis incidence of 60% 5 years following diagnosis for individuals not taking melatonin (participants in the control group). This is a relevant calculation considering the high-risk population recruited based on our inclusion criteria [46–49].An earlier study which included study participants with surgically removed lymph node metastases of malignant melanoma which showed that 31% (5 of 16 participants) of those treated with 20 mg of evening melatonin developed distant metastases compared to 71% (10 of 14 participants) of those not treated with melatonin [8].

Based on this previous research, the following assumptions are made:The number of participants in the melatonin group which will have developed distant metastases after 5 years: 30%The number of participants in the control group which will have developed distant metastases after 5 years: 60%.Alpha: 0.05Beta: 0.2Power: 80%Results: 42 participants must be included in each group, i.e., both the melatonin and the control group, in order to achieve statistical significance (Table 3). To obtain a safety margin in case some participants withdraw from the trial, we will strive after a group population of 50 participants per group.

**Table 3 Tab3:** Power calculation

**Melatonin, *****n***** = **	42
**Control, ***n*** = **	42
**Incidence, melatonin group**	30%
**Incidence, control group**	60%
**Alpha**	0.05
**Beta**	0.2
**Power**	0.8

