### Outcomes

The primary outcome is the number of patients which develop metastasis in the melatonin group vs. the control group. This will be evaluated as a relative risk (RR), with a 95% confidence interval. The secondary outcomes include the following: Overall survival 5 years from randomization in the melatonin group vs. control group, evaluated with Kaplan-Meier curves and the Log-rank test.Overall survival after detection of metastases in the melatonin group vs. control group, was evaluated with Kaplan-Meier curves and the Log-rank test.Hazard for having developed other cancers within 5 years from randomization in the melatonin group vs. control group, evaluated as Cox regression hazard ratio (HR).Number of patients with AE and SAE in the melatonin group vs. control group, assessed by CTCAE and evaluated as relative risk (RR) with a 95% confidence interval.

Other outcome measures:Interim analysis: number of patients developing metastasis within 3 years in the melatonin group vs. control group, evaluated as relative risk (RR), with 95% confidence interval.Interim analysis: overall survival in 3 years in the melatonin group vs. control group, evaluated with Kaplan-Meier curves and the Log-rank test.

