### Statistical analysis

We will be analyzing our data according to “intention to treat” where all participants randomized to either the melatonin or control group are included in the said group even if some terminate their participation in the trial or are excluded from the trial later on. We will at the same time analyze our data “per protocol” where the participants who terminate their participation during the trial or are noncompliant to melatonin treatment are excluded from the analysis.

To answer our primary and secondary objectives, we will use both the chi-square test and the Log-rank test of cumulative survival with associated 95% confidence intervals and *p*-values. Relative risk will be calculated as the probability of metastasis in the melatonin group divided by the risk of metastasis in the control group.

*P* values less than 0.05 will be considered significant, and all tests will be double-tailed, or two-sided.The Shapiro–Wilk test will be used to confirm if our continuous data is normally distributed.A Student’s *t*-test will be used to compare the differences in normally distributed continuous data within the melatonin and control groups, respectively. Data found not to be normally distributed data will be compared using the Mann–Whitney *U*-test.In order to compare the risk of death and metastasis between the melatonin and control group, we will also use a Cox Regression, adjusted for covariates such as tumor size, T category, cell type, presence of extra scleral growth, presence of extracellular matrix patterns, and BAP-1 expression.

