### Interim analyses

An interim analysis will take place 3 year after randomization of the last patient in the trial.

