### Management and auditing

The project management group for this trial will meet once or twice monthly to review trial conduct. This group is composed of a primary investigator and two research team members who will be providing day-to-day support to the trial. All group members will share responsibility for running the trial, with tasks such as recruiting and randomizing patients, conducting follow-ups, collecting data, and answering participants’ questions. They will communicate regularly via email and telephone in addition to the monthly meetings. No trial steering group is assigned for this trial; however, data is monitored by Karolinska Trial Alliance before launching the trial, at the beginning of the trial, after 1 month, after 3 months, and then every 6 months during the trial. The Swedish Medical Products Agency will review trial safety data and adherence to regulations once a year.

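### The p<0.05 rule for all tests also covers the 3-year interim; if either metastasis look may be claimed as an effect, the false-positive rate is about 7–9%, not 5%

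*Protocol article*

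**What the plan says.** All references are to the protocol article.

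- **Interim comparison.** Study objectives and hypothesis: once the last recruited patient has had 3 years of treatment, "we will compare the occurrence of metastases as well as the overall survival in the melatonin and the control group". Interim analyses repeats the timing: "An interim analysis will take place 3 year after randomization of the last patient in the trial".
- **Interim measures.** Outcomes lists, under other outcome measures, the "number of patients developing metastasis within 3 years in the melatonin group vs. control group", as a relative risk with 95% confidence interval, and 3-year overall survival by Kaplan–Meier and log-rank. The primary outcome uses the same estimator on metastasis, and the objective and hypothesis place it at 5 years.
- **Threshold.** Statistical analysis: P "values less than 0.05 will be considered significant, and all tests will be double-tailed, or two-sided". The interim is not exempted.
- **Sample size.** "Alpha: 0.05Beta: 0.2Power: 80"%, with 5-year metastasis rates of 30% on melatonin and 60% on control, giving 42 per group and a target of 50. No part of alpha is set aside for the interim.
- **Who knows what.** Randomization and allocation says that staff and participants know the assignment. Blinding says that outcome assessors are blinded during data analysis. Management and auditing states: "No trial steering group is assigned for this trial".

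**The concern.** Two between-arm comparisons of metastasis are planned, with the same estimator and the same threshold. Read literally, the rule lets a 3-year relative risk with p = 0.04 be reported as significant, whatever the 5-year result turns out to be. That gives the hypothesis that melatonin reduces metastasis two chances at 5% each, while the trial was sized for one.

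The second issue is exposure. Recruitment is complete at the interim, but some patients have up to 2 years of open treatment left. If results by arm reach them or the staff who follow them, adherence in the melatonin group or off-trial use in the control group could shift before the primary analysis.

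**Working it through.** **1. The plan's own figure.** Inputs from Sample size: 0.30 versus 0.60, two-sided alpha 0.05, power 80%. With pooled variance under the null and mean rate 0.45:

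n = [1.96·√(2·0.45·0.55) + 0.842·√(0.30·0.70 + 0.60·0.40)]² / 0.30² = 41.97, so 42 per group.

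Power is 80.0% with 42 and 86.6% with 50. The stated 42 therefore reproduces as a single-look calculation at the full 0.05.

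**2. Correlation of the two looks.** A patient with metastasis by year 3 also counts at year 5, so the two proportions are nested. With p3 and p5 the common rates under no effect:

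ρ = √[ p3(1 − p5) / (p5(1 − p3)) ].

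The article gives no 3-year rate. Under an assumed constant hazard, p3 = 1 − (1 − p5)^0.6. For p5 = 0.60: p3 = 1 − 0.40^0.6 = 0.423, and ρ = √[0.423·0.40 / (0.60·0.577)] = 0.70.

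**3. Chance of at least one significant result.** For bivariate normal statistics with correlation ρ, this is 1 − P(|Z₃| ≤ 1.96 and |Z₅| ≤ 1.96).

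| Common 5-year rate | 3-year rate, constant hazard | ρ | Either look p<0.05 |
|---|---|---|---|
| 30% | 19.3% | 0.75 | 8.1% |
| 45% | 30.1% | 0.73 | 8.2% |
| 60% | 42.3% | 0.70 | 8.3–8.4% |

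If instead 50% to 80% of the 5-year metastases appear by year 3, the range over these rates is 7.4–9.0%. Two independent looks would give 1 − 0.95² = 9.75%, which the nesting keeps out of reach in this approximation.

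**4. Simulated chi-square tests, no effect** (common rates 45% and 60%, constant hazard). With 50 per group: 8.6–8.8% for either look, against 5.2–5.6% for the 5-year test alone. With 42 per group: 9.2–9.8%, against 5.8–6.2%; part of that excess is the coarseness of the test in small groups rather than the second look.

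**5. If the interim uses all data at its calendar date.** Administrative information gives 3 to 4 years of recruitment; even accrual is assumed. Simulation with 50 per group (common rates 45% and 60%) gives a correlation of about 0.89–0.93 and an either-look rate of 7.1–7.6%.

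**6. What is still open at the interim.** Patients past 5 years are those randomized at least 2 years before the last one: (3 − 2)/3 = 33% with 3-year accrual and (4 − 2)/4 = 50% with 4-year accrual. So half to two thirds have not reached 5 years. Under constant hazard and the design rates, the share of 5-year metastases already seen is:

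| Accrual | Melatonin (30%) | Control (60%) |
|---|---|---|
| 3 years | 88% | 91% |
| 4 years | 91% | 93% |

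With 50 per group the design expects 15 + 30 = 45 events. About 15·0.12 + 30·0.09 = 4.5 (3-year accrual) or 15·0.09 + 30·0.07 = 3.5 (4-year accrual) are still to come.

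**7. Effect of the fix.** If the interim supports no claim and no stop, the final test stays at 0.05 with the power in step 1. If an interim claim needs p<0.001 and the final test is at 0.05, the step 3 calculation gives 5.00–5.05% overall across all scenarios. Holding exactly 5% would put the final level at 0.0495–0.0500; at 0.0498, power with 50 per group is 86.5% instead of 86.6%.

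**The case against.** The strongest reply is that the primary objective and hypothesis are fixed at 5 years, the interim stands among the other outcome measures, and no section lets it stop the trial or count as success. On that reading the 5-year test keeps its 5%. This stands: a reader might infer that the 5% error rate has already been lost, and the article does not support that. The level is unprotected rather than lost. What the reply does not remove is the threshold stated for all tests, which makes no exception for the interim.

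Boundaries, purpose and access rules may sit in the full protocol or an analysis plan that is not shown. That is fair, and the point does not rest on their absence. It rests on the stated threshold combined with a single-look sample size.

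Three further inferences go too far:

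- **That the open-label team itself runs the interim.** The first-person wording and the lack of a steering group suggest it, but no analyst is named, and Blinding says that outcome assessors are blinded during analysis.
- **That controls will cross over by buying melatonin.** Study setting and recruitment describes small packs of low-strength tablets at significant cost, and says that outside prescriptions can be detected. Nothing says that interim results will be disclosed to participants. Metastases are sought by scheduled 6-monthly imaging, and suspected ones are verified by biopsy, so reporting has limited influence on the primary outcome.
- **That interim overall survival should be added to the error rate.** Survival is a separate, secondary hypothesis and does not belong in the error rate for metastasis.

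**Conclusion.** The point holds in conditional form. The article states a rule under which either metastasis look may be called significant, and sizes the trial for one. If an effect may be claimed at either look, the false-positive rate is about 7–9%: 8.1–8.4% under constant hazard, 7.4–9.0% over wider assumptions about 3-year rates, and 7.1–7.6% if all data at the interim date are used. If the interim supports neither a claim nor a stop, the 5-year test stays at its nominal 5%.

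Exposure of the final comparison is a secondary and limited risk. Half to two thirds of patients have not reached 5 years at the interim, but only about 3 to 5 of 45 expected events remain, and the risk arises only if results by arm are released. Constant hazard and even accrual are assumptions throughout.

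**What to change.** Add a short paragraph to Interim analyses, and exempt the interim from the general threshold in Statistical analysis. Either of two wordings is enough:

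1. The interim is descriptive, with no efficacy claim and no stop for efficacy. The 5-year test keeps 0.05.
2. A claim at the interim requires p<0.001 (Haybittle–Peto), and the 5-year test is done at 0.05. The overall rate is then about 5.0%.

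In both cases, state that interim results by arm stay with the analyst, and are not given to trial staff or participants, until the last 5-year visit.

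The cost is the option of an interim efficacy claim at nominal p<0.05. No extra patients are needed and power is essentially unchanged. The text must be in place before the interim data are analysed, because a rule chosen afterwards would be post hoc.
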